### Statistical considerations

#### Sample size

With 107 participants per group (120 to account for a 10 % dropout rate) there is 80 % power to detect a difference in change in BMI of 0.5 SDS at the 5 % level of significance, with a standard deviation of 1.3 [48]. Of note, only 15/54 lifestyle studies included in a systematic review at the time of study design reported power calculations [11]. Subsequent meta-analysis of interventions has shown that even a change of −0.1 BMI SDS can lead to improvements in cardiovascular and metabolic outcomes [12]. It is hoped that even demonstrating smaller differences as this more recent literature has shown will still be important at a population level.

#### Data analyses

Statistical analyses will be performed using SAS version 9.3 (SAS Institute Inc. Cary NC). A general linear mixed model will be used to assess change from baseline measured at 6, 12, 18 and 24 months after initiating the intervention adjusting for age, gender, socioeconomic status, and ethnicity and degree of readiness for change. Means and standard deviations of changes from baseline in outcomes of interest, for both the raw and modelled data, will be presented.

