**Methods/Design:**

Whanau Pakari is an unblinded randomised controlled clinical trial comparing a 12 month intervention programme with standard practice, with 6 monthly assessments for 2 years, conducted in Taranaki, New Zealand (a region where 15.8 % of the population are indigenous). It specifically targets indigenous people and those in more deprived households.

Obese/overweight children and adolescents aged 5–16 years are eligible. Exclusion criteria are medical/psychological conditions leading to inability to undertake physical activity/participate in group sessions; those not “ready” to make lifestyle changes; and those without a committed family member.

Assessments of health parameters, dietary history, physical activity and overall health-related quality of life/psychological functioning are completed in the participant’s home. Fasting blood tests are obtained at baseline, 12 and 24 months.

The primary outcome is body mass index standard deviation score. Secondary outcomes include quality of life, dietary behaviour and physical activity, cardiovascular and metabolic profile (blood pressure, resting heart rate, waist circumference), glycaemic control (fasting glucose and glycated Haemoglobin), fasting insulin, and lipids.

A general linear mixed model will be used to assess change from baseline using the 6, 12, 18 and 24 month measures, adjusting for age, gender, socioeconomic status and ethnicity, and whether at the contemplative or preparation/action stages of readiness for change.

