### Participants

Children from the Taranaki region aged 5–16 years, with a body mass index (BMI) ≥98th centile, or those >91st centile with weight related comorbidities will be offered participation in the trial if referred to “Whanau Pakari”. These cut-offs are a modification of UK Cole data, and have been chosen as they are nationally accepted for use by the Ministry of Health for defining obesity and overweight respectively in the community for 0–5 years [20, 21]. (There are no nationally accepted growth charts or official cut-offs in use for >5 year old children currently.)

Exclusion criteria will be significant medical or psychological conditions leading to inability to undertake physical activity or participate in group sessions; those not “ready” to make lifestyle changes; and those without a committed family member (essential to support the family-based approach of the programme).

To optimise accessibility, referrals will be accepted from all health professionals within the community, including public health nurses in schools, and Maori health workers. Self-referrals will also be accepted (Fig. 1).

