### Randomisation

At baseline, there will be 2 assessments of RFC (given it is not known if a quantitative tool will be successful): the clinician’s subjective measure (ranked pre-contemplation, contemplation, preparation/action), and a specifically devised questionnaire using a 5-point Likert scale that is completed by the child (if > 11 years of age) and a second one for the parent. The RFC questionnaire was based on the original readiness to change questionnaire [15], focussing on beliefs and behaviour around three factors: weight, eating habits and activity levels. If the RFC ranking is scored in the contemplative or further along on either scale, then participants will be offered entry into the trial. We purposely set the bar low (i.e. below the preparation/action level) to assess whether degree of RFC predicts outcomes within those contemplative or above.

Patients will be assessed, consented, and entered into the trial prior to randomisation. Randomisation by minimisation (using age and ethnicity) will be conducted using the Minim randomisation computer programme which maintains approximate balance in the 2 arms for age and ethnicity but incorporates a random element so it cannot be predicted which study arm the subject will be allocated to.

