### Primary outcome

The primary outcome measure is the change in BMI SDS in the intervention group compared with the control group recorded at 6, 12, 18 and 24 months post enrolment.

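### The primary model analyses change in BMI SDS without adjusting for baseline BMI SDS: valid, but less precise than it could be at no cost

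*Protocol article*

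**What the plan says.** Under Primary outcome: "The primary outcome measure is the change in BMI SDS in the intervention group compared with the control group", at 6, 12, 18 and 24 months. Under Data analyses: "A general linear mixed model will be used to assess change from baseline measured at 6, 12, 18 and 24 months", and then the covariates, "adjusting for age, gender, socioeconomic status, and ethnicity and degree of readiness for change". The Methods/Design part of the Abstract gives the same set: "adjusting for age, gender, socioeconomic status and ethnicity, and whether at the contemplative or preparation/action stages of readiness for change". Neither list contains the baseline value of the outcome, and neither place says that baseline enters the model as one of the repeated responses.

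The Randomisation section names the balancing factors: "Randomisation by minimisation (using age and ethnicity". It also says that assessment comes before randomisation. Table 2 includes height and weight at baseline, and eligibility itself rests on BMI: "with a body mass index (BMI) ≥98th centile, or those >91st centile with weight related comorbidities". Baseline BMI SDS is therefore known for every child before allocation.

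**The concern.** The baseline value of a continuous outcome is often its strongest predictor. Subtracting it fixes the coefficient of baseline at 1, whereas a baseline-adjusted model estimates that coefficient. Whenever the true slope of follow-up on baseline is not 1, the change score carries avoidable noise.

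The listed covariates are unlikely to make up for this. BMI SDS is already standardised for age and sex against the reference data named under Calculations, so age and gender say little about how far above the norm a child starts. Minimisation does not use baseline BMI SDS either. Entry has a lower BMI limit but no stated upper one, so starting severity may vary widely.

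What is at stake is the width of the confidence interval for the primary comparison. This matters more here because the Sample size section hopes to show differences smaller than the 0.5 SDS that the trial was sized for.

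**Working it through.** **Inputs from the article (Sample size).** Evaluable group size 107, recruited group size 120 after allowing for dropout of one in ten. Power and target difference: "there is 80 % power to detect a difference in change in BMI of 0.5 SDS". The test level is 5 % and the SD is 1.3. Two-sided testing is assumed, because it reproduces the stated number. The correlation r between baseline and follow-up BMI SDS is not given, so a range of 0.5 to 0.9 is assumed.

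**The article's own figure.** n per group = 2 × (1.96 + 0.8416)² × 1.3² / 0.5² = 2 × 7.849 × 1.69 / 0.25 = 106.1, rounded up to 107. The standard error at 107 per group is 1.3 × √(2/107) = 0.1777. Power is Φ(0.5/0.1777 − 1.96) = 80.3 %. Dropout: 107/0.9 = 118.9, so 119, against 120 stated. The sample size reproduces.

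**Effect of adjustment.** Let the SD at baseline and follow-up be σ at both times.

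- Change score: variance per child 2σ²(1−r).
- Baseline-adjusted: variance per child σ²(1−r²).
- Ratio: (1−r²) / [2(1−r)] = (1+r)/2. It does not depend on σ.

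With 1.3 as the SD of change, the adjusted residual SD is 1.3 × √((1+r)/2):

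| r | Variance ratio | Residual SD | SE at 107 per group | Power at 107 per group | n per group for 80 % |
|---|---|---|---|---|---|
| unadjusted | 1.00 | 1.300 | 0.1777 | 80.3 % | 107 |
| 0.5 | 0.75 | 1.126 | 0.1539 | 90.1 % | 80 |
| 0.7 | 0.85 | 1.199 | 0.1639 | 86.2 % | 91 |
| 0.8 | 0.90 | 1.233 | 0.1686 | 84.3 % | 96 |
| 0.9 | 0.95 | 1.267 | 0.1732 | 82.3 % | 101 |

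With unequal SDs σ0 (baseline) and σ1 (follow-up), the excess variance of the change score is (σ0 − rσ1)². This is never negative, and is zero only when the slope of follow-up on baseline is 1.

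**The same loss seen as conditional bias.** If the arms differ at baseline by D, the change-score estimate equals the adjusted estimate minus (1−r)D. An illustrative imbalance of 0.2 SDS shifts it by 0.10 at r = 0.5, 0.04 at r = 0.8 and 0.02 at r = 0.9.

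This is not an extra term. With n per arm, D has variance 2σ²/n, so the shift contributes (2σ²/n)(1−r)². Adding the adjusted variance (2σ²/n)(1−r²) gives (2σ²/n) × 2(1−r), which is exactly the change-score variance.

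**Simulation check.** 8,000 trials were simulated at each of r = 0.5, 0.8 and 0.9, with 107 per group. Adjusted-to-unadjusted variance ratios were 0.76, 0.90 and 0.96. Power rose from about 80 % to 89 %, 84 % and 82 %. The slope of the change-score estimate on D was −0.50, −0.20 and −0.10, against about 0 after adjustment. The mean estimate was about −0.50, the true value, with and without adjustment.

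**The case against.** A journal article condenses the protocol, and an analysis plan that is not shown may include baseline. The Data analyses wording does not strictly exclude a longitudinal model with baseline as a response. The stated analysis is valid and reaches its stated power. If r is 0.9 or more, the gain is at most 5 % of the variance.

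Most of this stands as a limit on size. It does not remove the point: the article gives an explicit covariate list twice and describes the response as change at the four post-baseline visits. That is a stated choice rather than silence.

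A reader might also infer more than the documents support:

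- *That the treatment effect is biased or type I error inflated.* It is not, over randomisations. The shift is conditional on the imbalance that happens to occur.
- *That entry above a BMI threshold distorts the comparison through regression to the mean.* This affects both randomised arms equally in expectation and cancels in the difference.
- *That chance imbalance is a second harm on top of lost precision.* The identity above shows that it is the same quantity.
- *That a likely size of imbalance can be stated.* The article gives no baseline SD. A guess such as 0.6 cannot go with an SD of change of 1.3 under equal variances, since the SD of change could then be at most 2 × 0.6 = 1.2.
- *That the shift should be judged only against 0.1 SDS.* The article cites that value from later literature; the trial was sized for 0.5 SDS.

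**Conclusion.** The omission is real and worth correcting, as a loss of efficiency in a valid primary analysis. Over the assumed range r = 0.5 to 0.9, adjustment lowers the variance of the treatment effect by 25 % to 5 % and raises power at 107 per group from 80 % to between 90 % and 82 %. It also removes the dependence of the estimate on chance baseline imbalance.

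The figures assume equal variances at baseline and follow-up, a single follow-up visit and no other covariates; r may differ between visits. The power figures also take 1.3 as the SD of change. If 1.3 is also the SD of BMI SDS at each visit, the implied r is 0.5. If r is higher, an SD of change of 1.3 implies a wider spread of BMI SDS: 1.3/√(2(1−r)) is 2.06 at r = 0.8. The omission itself is certain from the text; its size depends on r, which the article does not give.

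**What to change.** Before the outcome data are analysed, add baseline BMI SDS as a fixed effect in the primary mixed model, with baseline-by-visit terms so that its coefficient can differ across 6, 12, 18 and 24 months. For each continuous secondary outcome, add that outcome's own baseline value in the same way. If a longitudinal model with baseline as a response and a common baseline mean across arms is intended instead, say so explicitly.

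The cost is one line in the analysis plan, plus a note that the covariate list extends the published one. No further data or participants are needed.

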#### Baseline characteristics

Baseline characteristics will be summarised using descriptive statistics. Continuous variables will be described as numbers of observed and missing values, mean, standard deviation, median, minimum and maximum. Categorical variables will be described as frequencies and percentages.

#### Treatment effects

Analyses will be performed on the intended to treat population. Reporting will adhere to the CONSORT guidelines for reporting parallel group randomised trials [13].

## Discussion

Whanau Pakari is expected to provide important new knowledge to the area of child obesity. This will be achieved with its focus on an indigenous group at increased risk for obesity and its resulting comorbidities, and through its engagement with the community to increase acceptability of the programme. It is likely to inform these areas in a robust manner if high participation is achieved and maintained.

This randomised controlled trial is unique in three key ways. First, it is assessing a mainstream multi-disciplinary clinical service that has evolved to specifically ensure accessibility and appropriateness for Indigenous people. Whanau Pakari is a community “real life” intervention programme resulting out of a clinical need, and has the potential to answer critical questions in relation to delivery of interventions in this area. Secondly, Whanau Pakari utilises a home-visit model which replaces hospital medical assessments, therefore “de-medicalising” obesity assessments. The family-based home model is likely to appeal to many ethnic groups who resist the hospital-based mainstream clinical models currently operating in most areas. Thirdly, Whanau Pakari will only include those considered potentially ready for change, and will investigate whether the level of “readiness” to make lifestyle changes predicts improved outcomes in intervention programmes. If the RFC measures provide a reliable and valid measure of outcome success, then the development of paired interventions around motivation for change for those in earlier stages of change followed by direct interventions for those in later stages could result in less programme dropout as well as being a more efficient and cost effective utilisation of limited resource.

A limitation of this study is the use of self-report for Tanner pubertal stage. Previous literature has demonstrated that obese girls tend to overestimate breast size and obese males stage of pubic hair development more than their non-obese counterparts [49]. However, we did not believe it was appropriate to undertake pubertal examination within the home setting, and it was determined this would be a more appropriate cut-off for pre-pubertal and pubertal status than an arbitrary age for males and females.

Weight-related comorbidities are a particular concern in child obesity, given the long-lasting effects of these conditions [50]. Past meta-analysis highlighted that a BMI SDS reduction of −0.1 led to significant improvements in multiple cardiovascular and metabolic outcomes over time [12]. BMI, in conjunction with waist circumference, WHtR, fasting lipids, glucose and insulin, and blood pressure (all being measured at intervals over an extended period of follow-up) will provide a comprehensive assessment of cardiovascular and metabolic outcomes long-term.

Whilst there has been a shifting focus toward early obesity intervention targeting critical periods of human development, there is still a need for an effective intervention programme to provide assistance for those children and adolescents who are already obese. This research aligns with the Ministry of Health’s clinical guidelines for weight management in children and young people [7], and addresses barriers to accessing services and programmes identified by the Office of the Auditor General’s performance audit into child obesity [51].

In summary, this trial will determine if this unique multi-disciplinary intervention will result in improved health outcomes, especially among Maori. It will also investigate whether there is an indication that being at the preparation/action stages of RFC compared to those in the contemplative stage results in improved success in intervention programmes. As translational research, it will inform the New Zealand Ministry of Health regarding ways to combat child and adolescent obesity. It is hoped this study will lead to prevention of the adult associated comorbidities of child obesity into later life for some individuals, thereby reducing morbidity, particularly for those most vulnerable in our population.

## Abbreviations

ANZCTR: Australian New Zealand Clinical Trials Registry
OECD: Organisation for Economic Cooperation and Development
CONSORT: Consolidated Standards of Reporting Trials
RFC: Readiness for change
BMI: Body mass index
HbA1c: glycated Haemoglobin
SDS: standard deviation score
WHtR: Waist height ratio
Peds QL: Pediatric Quality of Life
CBCL: Child Behaviour Checklist
C-PAQ: Children’s Physical Activity Questionnaire
CDQ: Children’s Dietary Questionnaire
